# 1. Introduction

The aim of this study is to determine whether protection from COVID-19 vaccination wanes after the first SARS-CoV-2 vaccine dose. At present, the vaccination programme in the UK uses two dose regimens of the Pfizer-BioNTech (BNT162b2) and the Oxford-AstraZeneca (ChAdOx1) vaccines. Whilst Moderna vaccine is now available in the UK, we will not include it in this analysis due to later start date and lack of follow-up data coverage. We theorise the vaccination programme as a natural experiment which has impacts that directly arise from the vaccination itself, as well as behavioural and other responses that occur as a consequence of broader programmatic effects - for example, being asked not to attend for vaccination if symptomatic and being reminded about protective behaviours to avoid infection.

We will use pseudonymised individual level linked routinely collected primary, laboratory and vaccination healthcare data across the UK nations. All data and analyses will be hosted within a trusted research environment within each nation. Pooled estimates will be calculated across the UK nations.

# 2. Aims and objectives

## 2.1 Aims

To assess the relationship between time since receiving the first vaccine dose and second dose (of the Pfizer-BioNTech and Oxford-AZ vaccines) compared to unvaccinated and partially vaccinated people, and effectiveness of SARS-CoV-2 vaccines against COVID-19 hospitalisation and death.

## 2.2 Objectives

We seek to:

1. Estimate vaccine effectiveness against the composite outcome of COVID-19 hospitalisation/death as a function of time since first SARS-CoV-2 vaccine dose and pool these estimates for the whole UK population.
2. Assess if vaccine effectiveness as a function of time since first vaccine dose differs by vaccine type, age group and sex.

# 3. Study Design

## 3.1 Study design

The primary study design is an open prospective cohort study with risk-set matching to emulate a ‘target trial’ comparing outcomes amongst first dose vaccinated (partially vaccinated) to people who have not yet been vaccinated [1-3]. To maximise statistical power, we will conduct secondary analyses using the entire study population.

The time period for the study will begin on the first date of vaccine administration in each UK nation, 8^th^ December 2020, and will end on the 30^th^ April 2021.

## 3.2 Setting

UK

## 3.3 Population

Individuals registered in General Practices (GPs) across the UK (~5.3 million for England, approx. 1.4 million for Northern Ireland, ~ 5.4 million for Scotland and ~3.1million for Wales).

## 3.4 Data sources

| **Data** | **Descriptive** | **England** | **Northern Ireland** | **Scotland** | **Wales** |
| --- | --- | --- | --- | --- | --- |
| Primary care data | General Practices (GPs) data for information on demographics, other population characteristics and vaccination data. | RCGP | NA | EAVE II – All GPs in Scotland | Welsh Longitudinal General Practice (WLGP) |
| Vaccination data | COVID-19 vaccines administered in national vaccination centres | GPs and the National Immunisation Management Service (NIMS) | GPs and Health and Social Care (HSC) Trusts via VMS | GPs and Turas Vaccination Management Tool (TVMT) | COVID Vaccination Data (CVVD) population from the all Wales Immunisation System (WIS) |
| Laboratory test data | RT-PCR laboratory confirmed SARS-CoV-2 infection | NHS Digital | Pillar 1 dataset from Laboratory Information System (LIS) and Pillar 2 dataset from NHS Digital | Electronic Communication of Surveillance in Scotland (ECOSS) database | Pillar 1 and 2 data from all NHS and private laboratories within the PATD data source. There is also national lateral flow testing data in CVLF |
| Hospitalisations | COVID-19 hospital admissions | Hospital Episode Statistics (HES), which are the long-term validated record; and Secondary Uses Services (SUS) which is an extract of contemporary operational data which after validation will become HES | Admissions and discharge dataset | Scottish Morbidity Record (SMR) 01 and Rapid Preliminary Inpatient Data (RAPID) | Patient Episode Database for Wales (PEDW) |
| Deaths | COVID-19 deaths | NHS Digital and Office for National Statistics (ONS) | National Health Applications and Infrastructure Services (NHAIS) and the Northern Ireland Statistics and Research Agency (NISRA) death data | National Records of Scotland (NRS) death data | National Population Spine (Welsh Demographic Service – WDSD), ONS death data (ADDE and ADDD) and a national NHS master patient index record (Consolidated Death Data Source – CDDS) |

## 3.5 Inclusion/exclusion criteria

Exclusion criteria:

- Age 17 or less at the study start date (8^th^ December 2020)
- Deceased prior to the study start date (8^th^ December 2020)
- Those living in an elderly care home (household with more than 10 people and an average age of over 65 as proxy)

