**Table 1: Data items/variables and data sources**

| **Data category** | **Data item** | **England** | **Northern Ireland** | **Scotland** | **Wales** |
| --- | --- | --- | --- | --- | --- |
| Demographic | Sex | GP | NHAIS | GP | C19_COHORT20 |
|  | Age | GP | NHAIS | GP | C19_COHORT20 |
| Socioeconomic status (SES) | IMD, SIMD, NIMDM, WIMD | Post code to IMD | NHAIS | GP | C19_COHORT20 |
| Other characteristics | Body Mass Index (BMI) | GP | GP | GP | WLGP, QCOVID |
|  | Smoking | GP | GP | GP | WLGP |
|  | Blood Pressure | GP | NA | GP | WLGP |
| Geographic | Type of settlement (urban/rural) | GP | NHAIS | GP | C19_COHORT20 |
|  | Local authority | GP | NHAIS | GP | C19_COHORT20 |
| Type of residence | Private housing, care home or social housing | GP | NHAIS | GP | C19_COHORT20, CARE |
| Clinical diagnoses | Underlying conditions  (e.g., asthma, cardiac disease etc.) | GP |  | GP | GP, WLGP, PEDW, CVSP, QCOVID, WDDS |
| Household information | Number of people in household, Average age of household (to create proxy for elderly care home) |  |  | Household identifier registry from CHI | C19_COHORT20, CARE |
| Vaccinations | Vaccine type | GP, NIMS | GP, HSC Trusts via VMS | GP, TVMT | CVVD |
|  | Vaccine dose | GP, NIMS | GP, HSC Trusts via VMS | GP, TVMT | CVVD |
|  | Vaccination date | GP, NIMS | GP, HSC Trusts via VMS | GP, TVMT | CVVD |
| Laboratory tests | RT-PCR SARS-CoV-2 test result | GP, Pillar 1&2  SGSS, PHE | Pillar 1 dataset from LIS, Pillar 2 dataset from NHS Digital | ECOSS | PATD (Pillar 1, 2, & 3 data from all NHS and private labs), CVLF testing and results data |
|  | Date of RT-PCR SARS-CoV-2 test |  |  |  |  |
|  | Genome sequencing data |  |  |  |  |
| Secondary care | Hospital admission | GP, SUS | Admissions and discharge dataset | SMR01 | PEDW |
|  | Admission ICD-10 code | GP, SUS | Admissions and discharge dataset | SMR01 | PEDW |
| Mortality | Deaths | GP, ONS, SSRS | National Health Applications and Infrastructure Services (NHAIS) and the Northern Ireland Statistics and Research Agency (NISRA) death data | NRS | C19_COHORT20_MORTALITY |

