### 5.5.2 Matched analysis

To create control groups for our primary analysis, we will emulate a ‘target trial’. We will do this by conducting 1:1 risk-set matching to identify individuals who had not yet become exposed (i.e. remained unvaccinated) on the date an exposed person received their vaccine dose. We will do this using a time-varying propensity score matching algorithm, by fitting separate propensity score models by month.

Due to the strong confounding effect of living in an elderly care home (arising from the targeted vaccination of these residents and their high risks of COVID-19 harms) and the lack of available controls, we will exclude people whose household had more than 10 people with an average age of 65 years and over. This will be used as a proxy for those living in an elderly care home.

We will incorporate the following characteristics into the time-varying propensity score model: sex, age (grouped in 5 year bands), SES, number of risk factors (grouped), number of previous SARS-CoV-2 tests pre-vaccination era (grouped), geography (local authority level), urban-rural settlement, average household age, number of people in household (grouped), smoker indicator, BMI (grouped), presence in hospital status (hospitalised for any reason 4 weeks prior to monthly time-period) and previous positive test indicator (tested positive previous to monthly time-period). Individuals will then be matched using exact matching based on the propensity score in 1% bands, local authority, and age (exact age in years, truncated up to 100 years). The adequacy of the matching will be assessed by checking for imbalance of the individual covariates and the individual risk groups across exposure groups.

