| Cirrhosis | | | 3279 (0.2%) | | 6106 (0.7%) | | 14366 (0.8%) | |  | |  |
| Congenital heart disease | | | 3598 (0.2%) | | 10123 (1.2%) | | 24413 (1.4%) | |  | |  |
| COPD | | | 9734 (0.6%) | | 33608 (3.9%) | | 90563 (5.1%) | |  | |  |
| Dementia | | | 2350 (0.1%) | | 7411 (0.9%) | | 17478 (1.0%) | |  | |  |
| Diabetes type 1 | | | 2046 (0.1%) | | 5554 (0.6%) | | 14921 (0.8%) | |  | |  |
| Diabetes type 2 | | | 16798 (1.0%) | | 76948 (8.9%) | | 167878 (9.5%) | |  | |  |
| Epilepsy | | | 8910 (0.5%) | | 12308 (1.4%) | | 43449 (2.5%) | |  | |  |
| Fracture | | | 51152 (2.9%) | | 40527 (4.7%) | | 97860 (5.5%) | |  | |  |
| Neurological disorder | | | 1386 (0.1%) | | 4300 (0.5%) | | 12602 (0.7%) | |  | |  |
| Parkinson’s | | | 576 (0.0%) | | 2403 (0.3%) | | 6063 (0.3%) | |  | |  |
| Pulmonary hypertension | | | 724 (0.0%) | | 1596 (0.2%) | | 6510 (0.4%) | |  | |  |
| Pulmonary rare | | | 1436 (0.1%) | | 5635 (0.7%) | | 16043 (0.9%) | |  | |  |
| Peripheral vascular disease | | | 3373 (0.2%) | | 11786 (1.4%) | | 28862 (1.6%) | |  | |  |
| Rheumatoid arthritis or SLE | | | 3455 (0.2%) | | 12601 (1.5%) | | 31283 (1.8%) | |  | |  |
| Respiratory cancer | | | 1192 (0.1%) | | 2461 (0.3%) | | 7260 (0.4%) | |  | |  |
| Severe mental illness | | | 150214 (8.6%) | | 121762 (14.1%) | | 267033 (15.1%) | |  | |  |
| Sickle cell disease | | | 391 (0.0%) | | 763 (0.1%) | | 1904 (0.1%) | |  | |  |
| Stroke/TIA | | | 7729 (0.4%) | | 31281 (3.6%) | | 79952 (4.5%) | |  | |  |
| Thrombosis or pulmonary embolus | | | 7879 (0.5%) | | 17365 (2.0%) | | 50876 (2.9%) | |  | |  |
| Care housing category | Care home | 996 (0.1%) | | 4547 (0.5%) | | 2474 (0.1%) | |  | |  | |
|  | Homeless | 2221 (0.1%) | | 355 (0.0%) | | 1424 (0.1%) | |  | |  | |
| Learning disability or Down's | Learning disability | 22384 (1.3%) | | 9518 (1.1%) | | 34498 (2.0%) | |  | |  | |
|  | Down's | 113 (0.0%) | | 360 (0.0%) | | 1198 (0.1%) | |  | |  | |
| Kidney disease | CKD5 without dialysis or transplant | 7523 (0.4%) | | 37526 (4.3%) | | 103489 (5.9%) | |  | |  | |
|  | CKD5 with dialysis | 537 (0.0%) | | 1204 (0.1%) | | 4331 (0.2%) | |  | |  | |
|  | CKD with transplant | 383 (0.0%) | | 1211 (0.1%) | | 3103 (0.2%) | |  | |  | |

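### The elderly care-home exclusion uses household size and mean age alone, leaves recorded care-home residents in the cohort, and ignores a residence-type item listed for all four nations

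*SAP*

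**What the plan says.** Section 3.5 excludes elderly care-home residents, identified by a "household with more than 10 people and an average age of over 65 as proxy". Section 4.2 builds the same variable. Section 5.5.2 gives the reason, "Due to the strong confounding effect of living in an elderly care home", and adds that few controls are available. There the rule is to "exclude people whose household had more than 10 people with an average age of 65 years and over", so the boundary at a mean age of exactly 65 differs from 3.5 and 4.2.

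Table 1 has a row for "Number of people in household, Average age of household (to create proxy for elderly care home". It names a source for Scotland and for Wales; the England and Northern Ireland cells are empty. A separate row, type of residence, is described as "Private housing, care home or social housing" and has a source in all four nations.

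The propensity model in 5.5.2 includes average household age and grouped household size, and matching is exact on age in years and local authority. Residence type is not named in the exclusion criteria, the confounder list (5.3), the propensity model, the matching or the whole-cohort adjustment (5.5.3).

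The descriptive table in 5.6.1 is headed as excluding elderly care-home residents. Its care-housing row reads "Care home | 996 (0.1%) | | 4547 (0.5%) | | 2474 (0.1"%), and a footnote says that all QCOVID care-home types are counted.

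**The concern.** The plan treats care-home residence as a confounder strong enough to justify exclusion, and then identifies residents indirectly although a direct item is listed. Residents missed by the proxy stay in the analysis. If they are more common among vaccine recipients than among controls of the same age and area, and at higher risk of COVID-19 hospitalisation or death, the RR moves towards 1 and effectiveness is understated.

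A modest bias could matter because section 5.5.2 compares the point estimate with an RR of 0.5. The example event counts from day 14 in 5.6.2, in arms of equal size, give 541/1,029 = 0.53 for both vaccines and 238/488 = 0.49 for BNT162b2. Both lie close to that line.

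The nations' results are to be pooled, so a rule with no listed inputs in two nations may be applied differently in each.

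**Working it through.** **Inputs, all from the SAP.** In the 5.6.1 table the Total row is not in the same column order as the other rows, so I took column totals as female plus male and refer to columns by those totals:
- Unvaccinated: 803,174 + 947,136 = 1,750,310
- First vaccinated column: 532,302 + 330,599 = 862,901
- Second vaccinated column: 911,365 + 855,982 = 1,767,347
- Sum: 4,380,558

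**Step 1. Reproduce the plan's percentages (care-home count / column total).**
- 996 / 1,750,310 = 0.057% (printed 0.1%)
- 4,547 / 862,901 = 0.527% (printed 0.5%)
- 2,474 / 1,767,347 = 0.140% (printed 0.1%)
- All: 996 + 4,547 + 2,474 = 8,017; 8,017 / 4,380,558 = 0.18%
- Both vaccinated columns: 7,021 / 2,630,248 = 0.267%

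**Step 2. How many the proxy cannot catch.** The rule needs a household of more than 10. The household-size rows add up to each column total, so everyone tabulated has a recorded size.
- 862,901 column, households of 11 or more: 850 + 217 + 55 = 1,122. Recorded residents in households of 10 or fewer are at least 4,547 − 1,122 = 3,425.
- 1,767,347 column: 1,301 + 222 + 171 = 1,694. At least 2,474 − 1,694 = 780.
- Together: at least 3,425 + 780 = 4,205.
- Unvaccinated column: 6,537 + 1,655 + 5,152 = 13,344 exceeds 996, so no bound follows.

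The two bounds assume the extreme case in which everyone in a household of 11 or more is a care-home resident, so the true numbers are probably higher.

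**Step 3. Share of the population with no listed household source.** From section 3.3: (5.3 + 1.4) / (5.3 + 1.4 + 5.4 + 3.1) = 6.7 / 15.2 = 44%.

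**Step 4. Illustrative crude inflation of the RR.** The SAP gives no risk ratio for residents, so k (resident risk divided by that of others) is an assumption, taken as 10 to 30. With p1 the resident share in the vaccinated and p0 = 0.00057 the share in the unvaccinated column:

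factor = [1 + p1(k − 1)] / [1 + p0(k − 1)]

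| Vaccinated group | p1 | k = 10 | k = 20 | k = 30 |
| --- | --- | --- | --- | --- |
| Both columns | 0.00267 | 1.02 | 1.04 | 1.06 |
| 862,901 column | 0.00527 | 1.04 | 1.09 | 1.13 |
| 1,767,347 column | 0.00140 | 1.01 | 1.02 | 1.02 |

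For example, in the 862,901 column at k = 30: (1 + 0.00527 × 29) / (1 + 0.00057 × 29) = 1.153 / 1.017 = 1.13.

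**The case against.** **The 8,017 may not be the people the rule targets.** The plan aims at elderly homes, while the table counts all QCOVID care-home types. There is no age breakdown and no count of those the proxy did remove. This stands: 8,017 is an upper bound and the proxy's failure rate is unknown.

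**The crude comparison is not the matched one.** The unvaccinated column has mean age 36, against 55.9 and 58.8 in the vaccinated columns. The matched arms both have mean age 57.9, and the 2,573,874 matched controls outnumber the 1,750,310 people in the unvaccinated column, so 0.057% is not the prevalence among controls. A reader might infer from 0.527% against 0.057% (a ratio of 9.3) a nine-fold imbalance in the primary analysis; the documents do not support that. Exact age matching and the household covariates absorb part of the difference. They do not equalise residence within an age, and a resident recorded in a small household looks like a community dweller to those covariates.

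**Balance checks may cover it.** Section 5.5.2 asks for balance on individual risk groups, and care housing is a QCOVID item, so the check might include it. But the matched table in 5.6.2 has no care-home row, so neither balance nor imbalance can be seen there.

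**Blank cells are not proof of missing data.** Table 1 leaves the PCR date blank for every nation although the outcome needs it, and uses NA elsewhere for an unavailable item. A reader might infer that the exclusion is impossible in England and Northern Ireland. The text supports only that no source is listed there, in a row that is filled for Scotland and Wales.

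**Waning.** A reader might infer that missed residents, if vaccinated early, would produce false waning. A stable confounder shifts the level of the RR in every period; a trend needs the residents' share to change with follow-up time, and nothing in the SAP shows this.

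**Conclusion.** The point holds in limited form. The exclusion as written is incomplete in the SAP's own example table: up to 8,017 recorded residents remain (0.18%), at least 4,205 of them vaccinated and out of the proxy's reach. A direct item listed for all four nations is unused, and the household inputs have no listed source for 44% of the stated population.

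Part of the confounding that the plan calls strong may remain, most likely biasing the RR towards 1. The crude size is about 2-6% for both vaccines together and 4-13% in the most affected column. This rests on an assumed 10- to 30-fold risk in residents and on the unmatched prevalences; the bias after matching cannot be computed from the SAP. The stronger statement, that the targeted confounding as a whole persists, goes beyond the evidence. An effect on apparent waning is possible but not shown. The difference between the two age cut-offs is clerical.

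**What to change.** In sections 3.5, 4.2 and 5.5.2, also exclude people with a recorded care-home residence from the type-of-residence item in Table 1, and keep the household proxy where household data exist. If only elderly homes are meant, restrict the flag to older residents and say so. State for each nation which source identifies residents, report how many people each rule removes, and use a single age cut-off in all three sections.

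The cost is one further flag from data already listed. At most 8,017 of 4,380,558 people (0.18%) would be lost in the example table, including some in non-elderly care settings unless the flag is restricted by age. The SAP says nothing about the accuracy of the residence item in any nation, which is a further reason to report removals by rule.

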# 4. Data and data validation

## 4.1 Data variables available

Table 1 lists the groupings of variables available for this study by data source. Exposure data are described in the vaccinations category. Outcome data are described in the secondary care, mortality, and laboratory tests categories. The rest of categories contain data on potential confounding factors and effect modifiers.

**Table 1: Data items/variables and data sources**

| **Data category** | **Data item** | **England** | **Northern Ireland** | **Scotland** | **Wales** |
| --- | --- | --- | --- | --- | --- |
| Demographic | Sex | GP | NHAIS | GP | C19_COHORT20 |
|  | Age | GP | NHAIS | GP | C19_COHORT20 |
| Socioeconomic status (SES) | IMD, SIMD, NIMDM, WIMD | Post code to IMD | NHAIS | GP | C19_COHORT20 |
| Other characteristics | Body Mass Index (BMI) | GP | GP | GP | WLGP, QCOVID |
|  | Smoking | GP | GP | GP | WLGP |
|  | Blood Pressure | GP | NA | GP | WLGP |
| Geographic | Type of settlement (urban/rural) | GP | NHAIS | GP | C19_COHORT20 |
|  | Local authority | GP | NHAIS | GP | C19_COHORT20 |
| Type of residence | Private housing, care home or social housing | GP | NHAIS | GP | C19_COHORT20, CARE |
| Clinical diagnoses | Underlying conditions  (e.g., asthma, cardiac disease etc.) | GP |  | GP | GP, WLGP, PEDW, CVSP, QCOVID, WDDS |
| Household information | Number of people in household, Average age of household (to create proxy for elderly care home) |  |  | Household identifier registry from CHI | C19_COHORT20, CARE |
| Vaccinations | Vaccine type | GP, NIMS | GP, HSC Trusts via VMS | GP, TVMT | CVVD |
|  | Vaccine dose | GP, NIMS | GP, HSC Trusts via VMS | GP, TVMT | CVVD |
|  | Vaccination date | GP, NIMS | GP, HSC Trusts via VMS | GP, TVMT | CVVD |
| Laboratory tests | RT-PCR SARS-CoV-2 test result | GP, Pillar 1&2  SGSS, PHE | Pillar 1 dataset from LIS, Pillar 2 dataset from NHS Digital | ECOSS | PATD (Pillar 1, 2, & 3 data from all NHS and private labs), CVLF testing and results data |
|  | Date of RT-PCR SARS-CoV-2 test |  |  |  |  |
|  | Genome sequencing data |  |  |  |  |
| Secondary care | Hospital admission | GP, SUS | Admissions and discharge dataset | SMR01 | PEDW |
|  | Admission ICD-10 code | GP, SUS | Admissions and discharge dataset | SMR01 | PEDW |
| Mortality | Deaths | GP, ONS, SSRS | National Health Applications and Infrastructure Services (NHAIS) and the Northern Ireland Statistics and Research Agency (NISRA) death data | NRS | C19_COHORT20_MORTALITY |

4.2 Constructed variables

- Time to event in weeks (0-13, 14-20, 21-27, 28-34, 35-41, 42-48, 49-55, 56-62, 63-69 and 70+ days from dose 1, extend to 70-76, 77+ if numbers allow)
- Number of Q Covid risk groups (0,1,2,3,4,5+)
- Number of PCR tests in the pre vaccination era (0,1,2,3-4, 5-9, 10+). This will serve as our proxy for healthcare workers where healthcare worker status is unknown.
- Elderly care home resident (defined as person from a household with more than 10 people and an average age of over 65)

## 4.3 Consistency and error checking

We will check for patterns of missingness and implausible values for all analytical variables being used, with a record maintained of reasons for exclusion of any records from analysis. In the case where a variable of interest has high levels of missingness, we will consider using alternative variables that are closely related as a proxy for these missing data.

# 5. Statistical analyses

## 5.1 Exposures of interest

For the first vaccine dose (partial vaccination), an individual will be defined as exposed from day 14 after receiving the first vaccine dose between the period of 8^th^ December 2020 and until the end of follow up on 30^th^ April 2021.

## 5.2 Outcomes of interest

The primary outcome will be a composite outcome of time to COVID-19 hospitalisation or death. COVID-19 hospitalisation will be defined as a RT-PCR confirmed positive test for SARS-CoV-2 in the 28 days prior to admission, or with ICD-10 code for COVID-19 (in any diagnostic position). COVID-19 deaths will be defined as COVID-19 as the underlying ICD-10 cause of death recorded on the death certificate, or death from any cause within 28 days of a positive RT-PCR test for SARS-CoV-2 infection.

Secondary outcomes will be the single outcomes of: a) COVID-19 hospitalisation (as defined above), and b) COVID-19 deaths.

## 5.3 Potential confounders

Age, sex, socio-economic status (SES), residential settlement measured by the urban/rural 6 fold classification (1 refers to large urban areas and 6 refers to small remote rural areas), household size, number and types of comorbidities commonly associated with COVID-19 illness (asthma, chronic kidney disease, liver cirrhosis, chronic neurological condition, heart failure, diabetes (type 1 and type 2), dementia, coronary heart disease), risk factors (smoking status, blood pressure, body mass index) and geography (local authority level).

